#### Secondary outcome measures

Secondary outcome measures include changes in concentrations of other components in breast milk, maternal health outcomes, infant growth and body composition, infant epigenetic markers (miRNA) and infant gut microbiota, as detailed below.

#### Breast milk components

In breast milk from baseline (6 weeks postpartum), 10 weeks postpartum and 14 weeks postpartum, we will determine the relative concentrations of metabolites and complex lipids using untargeted metabolomic and lipidomic profiling at Metabolon. At the same time points, we will measure breast milk concentrations of a network of 27 cytokines of relevance for the immune status (Human Cytokine Group 1 multiplex panel) with Luminex xMAP Technology on a Bio-Plex 200 system (Bio-Rad) at the Cellular and Molecular Imaging Facility at the NTNU. We will additionally measure concentrations of leptin, adiponectin, insulin, ghrelin and insulin-like growth factor-1 in breast milk at the same time points using ELISAs with a DS2 ELISA processing system (Dynex Technologies). We will profile miRNA after sample preparation for extracellular vesicle enrichment using a standard small RNA protocol and Illumina’s TruSeq SmallRNA Library Preparation Kit and sequencing with a NextSeq HighOutput flow cell on a NextSeq 500 Instrument (Illumina) at the Genomics Core Facility at NTNU.

#### Maternal outcomes

Maternal health outcome measures will be assessed at baseline, after 8 weeks (14 weeks postpartum) and after 6 months following the end of the intervention period (40 weeks postpartum) if not otherwise noted. Height will be measured only at baseline using a wall-mounted stadiometer. Body composition (total body mass, total fat mass, visceral fat mass, muscle mass and bone mass) will be estimated using bioelectrical impedance (InBody 770, Biospace CO, Korea). These measurements will be undertaken after an overnight fast, with the participants wearing light clothes and standing barefoot. BMI will be calculated as weight in kilograms divided by the square value of height in metres (kg/m^2^). Waist circumference will be measured using a metal measuring tape at the level of the belly button with the participant standing and after normal expiration.

Cardiorespiratory fitness will be measured as peak oxygen uptake during a maximum effort treadmill test using the gold standard direct expired gas analysis method (MetaLyzer II, Cortex, Germany). The test protocol will start with a 10 min warm-up and be individualised. We will report the average of the three highest consecutive 10 s measured as absolute (L/min) and relative (mL/min/kg) values. We will use the highest heart rate recorded throughout the exercise test to estimate the participant’s maximum heart rate.^21^

We will measure blood pressure with an automatic cuff (Welch Allyn, Germany) on the participants’ left arm after resting in a seated position for 15 min. We will obtain three measurements at 1 min intervals and report the average of these three measurements as diastolic and systolic blood pressure in mm Hg. We will additionally report the resting heart rate obtained by the same device.

We will sample maternal blood after an overnight fast and analyse the samples for blood lipids (total cholesterol, low-density lipoprotein cholesterol, high-density lipoprotein cholesterol, triglycerides), glucose, insulin C-peptide, high-sensitive C reactive protein and glycated haemoglobin concentrations at the St. Olav’s Hospital laboratory using their standard procedures. Additional blood will be stored for future analyses.

Participants will fill out study-specific questionnaires about their health and lifestyle, with questions on maternal background characteristics (eg, age, ethnicity and education), physical activity, medication use, gestational weight gain, infant birth weight, length, head circumference and sex. They will also complete the Psychological General Well-Being Index.^22^ We ask the participants to register their dietary intake using the FatSecret application for 4 days (out of which one is a weekend day), at baseline, in the last week of the intervention period and at 6 months after the end of the intervention period (40 weeks postpartum), and to share this information with the investigators. Participants will additionally report the type of food and supplements the infants are given at baseline, at the end of the intervention period (14 weeks postpartum), and at infant age 6 months, 12 months and 24 months. Participants who stop exclusively breast feeding during the study period will not be excluded from the study.

#### Infant outcomes

At baseline, after 4 weeks, 8 weeks and 6 months from the end of the intervention period, we will measure the infants’ weight and length and estimate their body composition. We will use a Seca 336 baby scale to measure weight and a Seca 2010 mobile measuring mat to measure length (Seca GmbH, Germany). The body composition of the infants will be estimated using bioimpedance (BioScan touch i8-nano, Maltron, UK). We will collect data from local health centres that offer surveillance of all infants in Norway, free of charge. These data will include weight, length/height and head circumference measurements when the infants are 4 and 6 weeks old and at 3, 4, 6, 8, 10, 12 and 24 months.

We will collect faecal samples from the infants at these ages: 6 weeks (baseline), 10 weeks, 14 weeks, 26 weeks, 40 weeks, 12 months and 24 months. The participants will be provided with a detailed description with photo illustrations. They will collect the samples into sterile cryoboxes before freezing them in their home freezer until transported to the laboratory. We plan to extract total faecal genomic DNA from the faecal samples using AllPrep Power Fecal DNA/RNA kits (Qiagen) and to undertake shotgun metagenomic sequencing with Illumina NovaSeq at the Genomics Facility, NTNU.

When the infants are 6 weeks (baseline) and 14 weeks (after 8 weeks), we will sample blood from their heels on a cellulose paper. These blood spots will dry completely at room temperature before storage in sterile, light-opaque plastic bags at −80°C until analysis. We will isolate total RNA from the dried blood spots and analyse for miRNA using the same miRNA sequencing described above for breast milk miRNA. We will focus, in particular, on miRNAs implicated in accelerating preadipocyte proliferation, insulin secretion by pancreatic beta-cells and glucose uptake by skeletal cells, which contribute to the pathological processes of obesity and type 2 diabetes^23^ and miRNAs linked to childhood obesity.^24^ Additional blood spots will be kept for later analyses.

#### Adherence

We will record adherence to the exercise programme as the number of sessions completed divided by the number of sessions scheduled (n = 25). To determine whether the participants have exercised with the prescribed intensity, we will calculate their average heart rate during the moderate-intensity sessions and their average heart rate during the second half of the high-intensity work bouts during the high-intensity interval sessions.

#### Sample size calculation

There is no prior research to guide the determination of clinically meaningful changes in the primary outcome measure. The sample size calculation was based on the observed effect of exercise training on the concentration of 3′SL in mouse milk, with an increase from 2500 nmol/mL (SD 200) to 2900 nmol/mL.^19^ For a two-tailed t-test to detect such a difference between groups in the level of this single HMO, with a statistical power of 0.90 and an alpha risk of 0.05, we will need five participants per group. Given the expected higher variation in humans, multivariate analyses and a predictable dropout rate of ~15%, we aim to include at least 62 women in the trial.

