### Randomisation and allocation

Following screening and initial assessments, participants will be randomly allocated (1:1) after stratifying for gestational diabetes (yes/no) to the intervention or control groups. We will use a computer random number generator developed and administered at the Clinical Research Unit (Klinforsk), St. Olav’s Hospital, to randomly allocate participants. The allocation of participants is concealed until a participant is included. Block randomisation minimises any imbalance in group allocation, and the block sizes vary with the size of the blocks unknown to the researchers to maintain allocation concealment.

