#### Primary outcome measure

The primary outcome measure is change in the relative concentrations of breast milk 3′SL from baseline to after 8 weeks (14 weeks postpartum). We plan to do untargeted metabolomics using ultra-high-performance liquid chromatography tandem mass spectrometry (UPLC-MS/MS; positive mode), UPLC-MS/MS (negative mode) and gas chromatography-MS at Metabolon (USA).

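### The only stated power figure is wrong for the test it names (five per group gives 79%, not 90%) and does not describe the primary outcome; the target of 62 carries no power or detectable effect

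*Protocol article*

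**What the plan says.** The Sample size calculation section of the protocol article first acknowledges that no earlier research shows what change in the primary outcome would be clinically meaningful. It then takes its effect from exercise-trained mice, "with an increase from 2500 nmol/mL (SD 200) to 2900 nmol/mL", and sets out the test: "For a two-tailed t-test to detect such a difference between groups in the level of this single HMO". From this it concludes that "with a statistical power of 0.90 and an alpha risk of 0.05, we will need five participants per group".

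The enrolment target follows from a list of reasons: greater variation in humans, multivariate analyses, and "a predictable dropout rate of ~15"%. The result is that "we aim to include at least 62 women in the trial". No human SD, effect size or power goes with that number.

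The Primary outcome measure section defines a different quantity: "The primary outcome measure is change in the relative concentrations of breast milk" 3′SL, from baseline to 14 weeks postpartum, measured by untargeted metabolomics. Allocation is 1:1 (Randomisation and allocation).

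**The concern.** There are two problems of unequal weight.

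The lesser one is arithmetic. The section fixes every input to a standard calculation, and the stated sample size does not give the stated power for the test named.

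The greater one is what the calculation describes. Its 90% belongs to a ten-subject comparison of absolute levels with a mouse SD. The trial will compare changes in relative concentration in women, in groups about five times as large after dropout (26 against 5). An SD in nmol/mL for a level does not give the SD of a change in relative concentration, which also depends on the correlation between baseline and 14 weeks. The step from five per group to 62 in total is not derived, so the document does not say what size of effect the trial can detect on the one outcome tested at p < 0.05 without multiplicity adjustment.

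**Working it through.** **Inputs from the Sample size calculation section.** Difference 2900 − 2500 = 400 nmol/mL. SD 200, given with the 2500 value and taken here as common to both groups. Two-sided alpha 0.05, power 0.90, dropout 15%, total 62. Allocation is 1:1.

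**Standardised difference.** d = 400/200 = 2.0.

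**Reproducing five per group.** The normal approximation is n = 2(z₀.₉₇₅ + z₀.₉₀)²/d² = 2(1.960 + 1.2816)²/4 = 5.25 per group. A required sample size is rounded up, giving 6. At n = 5 the same approximation gives 88.5% power. So five is close to the normal-approximation answer but does not reach 90% even there.

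**Exact two-sided two-sample t-test.** Power is the probability that a noncentral t variable, with 2n − 2 degrees of freedom and noncentrality d√(n/2), exceeds the critical value in absolute size.

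| n per group | df | critical t | noncentrality | power |
|---|---|---|---|---|
| 5 | 8 | 2.306 | 3.162 | 79.1% |
| 6 | 10 | 2.228 | 3.464 | 87.6% |
| 7 | 12 | 2.179 | 3.742 | 92.9% |

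Seven per group are needed: 14 in total, and 14/0.85 = 16.5, so 17 after dropout. This is far below 62.

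**What 62 delivers.** 62 × 0.85 = 52.7, so about 26 per group. Solving the same power function for d:

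| n per group | d for 90% power | d for 80% power |
|---|---|---|
| 26 (after dropout) | 0.92 | 0.79 |
| 31 (no dropout) | 0.84 | 0.72 |

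These are in units of the SD of whatever is analysed.

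**Against the mouse effect.** The mouse rise is 400/2500 = 16%. With 26 per group and an unadjusted comparison of levels:
- 90% power needs SD ≤ 400/0.917 = 436 nmol/mL, that is, CV ≤ 436/2500 = about 17%.
- 80% power needs SD ≤ 400/0.792 = 505 nmol/mL, that is, CV ≤ 505/2500 = about 20%.

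The mouse CV is 200/2500 = 8%, so the 90% limit allows an SD about 2.2 times that in mice (436/200).

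**Illustration only.** The document gives no human CV and no baseline correlation. Power for a 16% difference with 26 per group, under assumed CVs and an assumed correlation of 0.7:

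| assumed CV | unadjusted level | change score (r = 0.7) | baseline-adjusted (r = 0.7) |
|---|---|---|---|
| 30% | 47% | 68% | 75% |
| 40% | 29% | 45% | 51% |
| 50% | 20% | 31% | 35% |

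The change-score SD is the level SD × √(2(1 − r)); the baseline-adjusted SD is the level SD × √(1 − r²).

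**The case against.** The strongest reply is that the error changes nothing in the trial. Nobody plans to enrol five per group; the figure is a starting point, and the corrected requirement of 17 lies well inside 62. That stands, and it limits the severity. It does not make the sentence correct. Other calculations come near 90% at five per group (a one-sided t-test 89.2%, a paired or one-sample t-test 90.9%), but the text names a two-tailed comparison between groups. Because several routes lead close to the stated figure, where the five came from is unknown and should not be asserted.

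A second reply is that the document is candid: it says that human data are lacking, names mice as the source, and gives greater human variation as a reason to enlarge the trial. This too stands, and it explains why no human effect was assumed. It does not prevent a statement of the detectable standardised difference, which needs only the number of completers, alpha and power.

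A third reply is that a standardised difference has no units, so the contrast between absolute and relative concentration matters less than it seems. That is partly right. The weight of the mismatch lies in carrying a mouse SD of a level over to the SD of a change in women.

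A reader might infer that the protocol claims 90% power for 62. It does not: the 0.90 is attached only to the mouse-based calculation. A reader might also infer from the illustrative table that the trial is underpowered. The document does not support that either, because those CVs and the correlation are assumptions; if the human CV is about 17% or less, 62 gives 90% power for the mouse-sized effect even without baseline adjustment.

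**Conclusion.** The point holds as a correction to one paragraph, of minor to moderate severity. For the test and inputs stated, five per group gives 79% power and seven are needed for 90%. This assumes a common SD of 200 and the exact two-sample t-test, and it leaves the enrolment target untouched.

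The more useful half is that the document's only power figure describes neither the primary outcome nor the planned sample size, and that 62 comes with no detectable effect. With 15% dropout spread evenly over the groups, the trial can detect about 0.92 SD with 90% power or 0.79 SD with 80%.

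It would go too far to say that a null result could not be interpreted: a confidence interval would still show which effects are excluded. What is missing is a planned effect to read that interval against.

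**What to change.** Reword the Sample size calculation paragraph as follows, with no change to enrolment, endpoint or analysis:

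1. Replace five with seven per group for 90% power, or keep five and state 79% power.
2. Say that the 90% refers only to the mouse-based calculation on an absolute level.
3. Add what 62 delivers: after 15% dropout, about 26 per group give 90% (80%) power for a between-group difference of about 0.92 (0.79) SD, where the SD is that of the primary outcome as analysed. Name that quantity: the change from baseline, or the baseline-adjusted 14-week value.
4. If the 16% mouse effect is kept as a reference, say that an unadjusted comparison of levels reaches 90% (80%) power for it only if the human CV is about 17% (20%) or less. Mark power at any higher CV as illustrative.

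The cost is one rewritten paragraph, and figures that read less favourably than the present ones.

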#### Statistical analyses

Our primary analysis will be completed according to the ‘intention-to-treat’ principle, using all obtained data irrespective of participant adherence to the intervention and completeness of outcome measures. No differences between groups are expected at baseline due to the randomised design. We will consider p value < 0.05 as statistically significant for our primary outcome measure. We will report Benjamini-Hochberg adjusted p values (q values) for the secondary outcome measures and consider q values < 0.05 statistically significant to decrease the false discovery rate due to multiple comparisons.

#### Multivariate analyses

We plan to use repeated measures analysis of variance simultaneous component analysis^25^ to determine multivariate changes in longitudinal profiling data (metabolomics, lipidomics and cytokines). Additionally, other bioinformatical analyses available during analyses will be considered. miRNA expression will be analysed by standardised bioinformatics pipelines as previously described.^26^ The limma and voom linear modelling framework^27^ will identify miRNAs with treatment-related longitudinal expression changes. Additionally, other bioinformatical analyses available during analyses will be considered. A taxonomic assignment that includes the abundance of different microbes within each microbiome from the infant microbiome will be used to calculate the alpha and beta diversity scores within and between periods. Differential abundance metrices and generalised linear mixed models (LMMs) will be used to estimate the fixed effects of alpha diversity of time on different clinical outcomes.

#### Univariate analyses

We plan to use LMMs for between-group comparisons of the maternal outcomes described and for the comparison of infant anthropometrics and body composition. Each model will include time and group×time interactions as fixed effect variables and subject (participant ID) as a random factor.^28^ In these analyses, we will consider the baseline values equal in both groups as there are no expected systematic differences between groups in RCTs. We will report estimates with 95% CIs and p values for group differences. In the case of non-normal model residuals, we will perform bootstrapping, transformations or non-parametric methods.

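### As methods are allocated, 3′SL and the milk hormones fall outside the only model that promises group estimates, CIs and p values; that model omits the randomisation stratum and leaves its fallback open

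*Protocol article*

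**What the plan says.** The Primary outcome measure section of the protocol article states: "The primary outcome measure is change in the relative concentrations of breast milk 3′SL from baseline to after 8 weeks (14 weeks postpartum". The same section gives the assay: "We plan to do untargeted metabolomics using ultra-high-performance liquid chromatography tandem mass spectrometry". So 3′SL is one variable in the metabolomics data.

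Statistical analyses sets the criterion: "We will consider p value < 0.05 as statistically significant for our primary outcome measure". Secondary outcomes are judged on Benjamini-Hochberg q values.

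Multivariate analyses assigns repeated measures ANOVA simultaneous component analysis (RM-ASCA) "to determine multivariate changes in longitudinal profiling data (metabolomics, lipidomics and cytokines".

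Univariate analyses gives the mixed model its scope: "We plan to use LMMs for between-group comparisons of the maternal outcomes described and for the comparison of infant anthropometrics and body composition". Time and group×time are the fixed effects, participant is random, and baseline is taken as equal in both groups. This section alone promises estimates with 95% CIs and p values for group differences. Its fallback reads: "In the case of non-normal model residuals, we will perform bootstrapping, transformations or non-parametric methods".

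Randomisation and allocation stratifies by gestational diabetes. Sample size calculation uses a two-tailed t-test on the level of the single oligosaccharide. Sensitivity analyses adds secretor-adjusted analyses of the milk data, without naming the model being adjusted.

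**The concern.** One p value decides this trial, and the article's allocation of methods does not lead to it. The method named for metabolomics describes patterns across many analytes; nothing in the article says that it will yield a group difference for 3′SL with its own interval and p value. The method that does yield those is assigned to other outcomes. The model behind the primary test could then be settled after the milk data have been seen.

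Two rules that the article does state would carry over if the mixed model were simply extended to milk. Its fixed effects leave out the factor used to stratify randomisation, and its fallback lets the analyst choose among three kinds of method once the residuals are known.

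**Working it through.** **1. Do the maternal outcomes include milk?** Three places bear on this.
- Secondary outcome measures lists "changes in concentrations of other components in breast milk, maternal health outcomes, infant growth and body composition", so milk components and maternal health are separate classes.
- Breast milk components and Maternal outcomes are separate sections.
- Their schedules differ. Milk is sampled at 6, 10 and 14 weeks postpartum. For the mothers, "Maternal health outcome measures will be assessed at baseline, after 8 weeks (14 weeks postpartum) and after 6 months" from the end of the intervention, that is, at 6, 14 and 40 weeks.

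On the article's own structure, milk is not a maternal outcome.

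**2. Method by outcome class**

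| Outcome | RM-ASCA | Mixed model |
|---|---|---|
| 3′SL (primary, metabolomics) | yes, by class | not named |
| Other metabolites, lipids, milk cytokines | yes | not named |
| Milk leptin, adiponectin, insulin, ghrelin, IGF-1 (ELISA) | not named | not named |
| Maternal health outcomes | no | yes |
| Infant anthropometrics and body composition | no | yes |

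Milk miRNA has its own method (limma/voom). The primary outcome has no univariate model, and the five ELISA hormones have no named method at all.

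**3. The only test tied to 3′SL: the sample size t-test.** Inputs: difference 2900 − 2500 = 400, SD 200, two-sided alpha 0.05, power 0.90.
- Normal approximation: n = 2 × (1.960 + 1.282)² × 200² / 400² = 5.25 per group, rounded up to 6.
- Exact t-test: 6.39, rounded up to 7.

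The stated five is slightly low but close. The recruitment target of 62 does not rest on it: 62 × 0.85 = 52.7, about 26 per group, gives 90% power for a standardised difference of 0.92 and 80% power for 0.79. None of this names the analysis model.

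**4. Precision at stake.** Let r be the baseline-to-14-week correlation and set the outcome variance to 1, equal at both times. A change score has variance 2(1 − r). A constrained-baseline model has residual variance 1 − r². The ratio is (1 − r²) / [2(1 − r)] = (1 + r)/2.

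| r (assumed) | 1 − r² | 2(1 − r) | Ratio | Reduction |
|---|---|---|---|---|
| 0.3 | 0.91 | 1.40 | 0.65 | 35% |
| 0.5 | 0.75 | 1.00 | 0.75 | 25% |
| 0.7 | 0.51 | 0.60 | 0.85 | 15% |
| 0.9 | 0.19 | 0.20 | 0.95 | 5% |

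**5. Type I error from an open choice.** Simulation with 26 per arm, lognormal data, log-SD 0.4, 0.6 and 0.8 (assumed), no group effect, 20,000 runs each:
- smallest of three p values (raw t, log t, Mann-Whitney): 0.067 to 0.072;
- raw t unless a residual normality test rejects, then one fixed alternative (log or rank): 0.050 to 0.054;
- the same trigger, then the better of log and rank: 0.060 to 0.062.

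**The case against.** The strongest reply is that this is a condensed article. A full protocol or analysis plan, not shown, may name the primary model, and an article may leave that to it. The two method sections state what is planned; neither says that its list is exhaustive. Other text points to a univariate primary test: one analyte, one interval, an unadjusted threshold of 0.05, and sizing on a single oligosaccharide.

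Much of this stands, and it rules out several stronger readings that a reader might infer.
- *That all metabolomics data, and so the primary test, go to RM-ASCA.* The article says neither that all such data go there nor that a univariate test of 3′SL is excluded.
- *That the t-test is a competing third analysis.* Sizing a later mixed model with a t-test is an ordinary simplification.
- *That the fallback inflates type I error to 0.07.* That figure requires picking on p values, whereas the stated trigger is non-normal residuals. As written, the fallback also does not reach 3′SL; it matters once the model is extended to milk.
- *That secretor adjustment is misplaced.* The article calls secretor status an important determinant of oligosaccharide abundance, but keeping it in sensitivity analysis is a legitimate choice.

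The reply does not remove the core. The article does more than stay silent: it allocates methods by class, and that allocation leaves the primary outcome out of the section that produces group estimates. The fixed effects and the three-way fallback are stated rules, not omitted detail.

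**Conclusion.** The point holds as a moderate defect of allocation and specification. The article leaves 3′SL and the milk hormones outside its only model promising estimates, CIs and p values; that model's fixed effects omit the gestational diabetes stratum; and its fallback is not fixed in advance. The first part rests on reading milk and maternal outcomes as separate classes, which the article's headings and schedules support.

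The main gain from correcting it is a deciding test fixed before the data are seen. The precision gain is real but of unknown size: 35% lower residual variance than a change score at r = 0.3, and 15% lower at r = 0.7. The comparison is with a change-score analysis that the article does not itself propose. Skewness, log-SD and r are assumptions. No stated figure changes, so a rating of must-fix would be too strong.

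**What to change.** Amend Univariate analyses as follows.
- Extend the constrained-baseline mixed model to 3′SL and the five milk hormones, using the 6, 10 and 14 week samples, with time, group×time and gestational diabetes as fixed effects and participant as a random effect. Add gestational diabetes to the other models in that section too.
- Name the group contrast in 3′SL at 14 weeks as the single primary test at 0.05, reported with its 95% CI.
- State the scale in advance, for example log relative abundance.
- Replace the three-way fallback with one: a participant-level bootstrap of the same model.
- Keep RM-ASCA as supportive for the profiling data.

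Secretor status may be moved into the primary model for precision, but this is optional.

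The cost is one paragraph of wording, with no new data, no change to the sample size and one extra model term. It should be dated before group-level milk results are seen. If an unpublished analysis plan already contains these choices, the article need only say so.

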### Trial status and modifications to the protocol after trial commencement

The first participant was included on 14 November 2022. As of 11 September 2023, we have included 21 participants. Recruitment is expected to continue until the end of 2024. The follow-up 6 months after the intervention period was added in February 2023. We added maternal bone mass as a secondary outcome measure in July 2023. We changed the time for recruitment from 5–6 weeks postpartum to 6–7 weeks postpartum in August 2023.

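### Infant growth to 24 months: a mixed model with participant as the random factor, followed as written, gives intervals that are too narrow at the latest ages

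*Protocol article*

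**What the plan says.** Univariate analyses gives one model form for the maternal outcomes and "for the comparison of infant anthropometrics and body composition". Its terms are: "Each model will include time and group×time interactions as fixed effect variables and subject (participant ID) as a random factor". Baseline is constrained: "we will consider the baseline values equal in both groups". The output is inferential: "We will report estimates with 95% CIs and p values for group differences". The one stated departure is "In the case of non-normal model residuals, we will perform bootstrapping, transformations or non-parametric methods".

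Infant outcomes describes two data streams. Laboratory weight, length and bioimpedance are taken "At baseline, after 4 weeks, 8 weeks and 6 months from the end of the intervention period", that is, at about 6, 10, 14 and 40 weeks of age. Health-centre records supply head circumference as well as weight and length/height, from "measurements when the infants are 4 and 6 weeks old and at 3, 4, 6, 8, 10, 12 and 24 months".

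The section names no random slope, residual correlation or age-specific variance. It does not say whether growth is analysed in raw units or as age-standardised scores, or whether the two streams enter one model.

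**The concern.** A participant random intercept with independent residuals is compound symmetry. That can be tolerable for three closely spaced visits. It is a poor description of growth from the first weeks to two years: measurements 4 weeks apart agree much more closely than measurements 22 months apart, and the spread of raw weight or length increases with age. With complete data the model attaches the same standard error to the group difference at every post-baseline age, so one pooled figure stands in for quantities that differ.

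At stake is the claim about infant growth, a secondary aim on which the Discussion places much weight. If the late-age SE is understated, chance differences at 12 or 24 months are declared too often. The Benjamini-Hochberg step in Statistical analyses takes the p values as valid, so it does not correct this.

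**Working it through.** The article calculates no figure for infant growth; its only sample-size figure concerns the primary outcome. There is therefore nothing of the plan's own to reproduce, and the check compares the SE the model would report with the SE that would be true.

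**Inputs from the article.** At least 62 women, 1:1 allocation, dropout about 15%: 62 × 0.85 = 52.7, so about 26 infants per arm. Equal-baseline constraint. Ages as listed in Infant outcomes.

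**Assumptions, not in the article.** Time as categories; complete data; SD at 24 months divided by SD at 6 weeks between 1.0 and 2.5; correlation between 6 weeks and 24 months between 0.30 and 0.79, falling with the age gap.

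**Formulas.** Let ρ be the intraclass correlation the random-intercept model settles on (average covariance ÷ average variance), and σ the pooled SD. With equal baselines, the estimated difference at age t is the observed difference at t minus ρ times the observed baseline difference.

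- Model SE = σ √[(1 − ρ²) × 2/26], the same at every t.
- True SE = √[(σ_t² + ρ²σ_0² − 2ρ r_t σ_0 σ_t) × 2/26], where r_t is the true correlation of age t with baseline.
- Type I error = 2[1 − Φ(1.96 × model SE/true SE)].

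**Example A: constant SD, as with z-scores.** Seven ages, SD 0.60 throughout, ρ = 0.79, r = 0.84 at 14 weeks and 0.58 at 24 months.

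- Model SE = 0.60 × √(0.376/13) = 0.102.
- True SE at 24 months = √[(0.36 + 0.225 − 0.330)/13] = 0.140. Ratio 0.73, type I error 15%.
- True SE at 14 weeks = √[(0.36 + 0.225 − 0.478)/13] = 0.091. Ratio about 1.13.

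**Example B: SD doubles from 0.60 to 1.20.** Seven ages, pooled SD 0.913, ρ = 0.805, r = 0.695 at 24 months.

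- Model SE = 0.913 × √(0.352/13) = 0.150.
- True SE at 24 months = √[(1.44 + 0.233 − 0.806)/13] = 0.258. Ratio 0.58, type I error 25%.

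**Range over the assumptions (model SE ÷ true SE).**

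| Setting | 14 weeks | Last age | Type I error, last age |
|---|---|---|---|
| SD ratio 1.0 | 1.02–1.13 | 0.66–0.74 (24 months) | 14–19% |
| SD ratio 1.5 | 1.11–1.24 | 0.57–0.66 (24 months) | 20–26% |
| SD ratio 2.0–2.5 | 1.18–1.34; up to 1.48 if SD rises linearly with age | 0.46–0.61 (24 months) | 23–36% |
| Laboratory visits only | about 1.05–1.1 | 0.63–0.79 (40 weeks) | 12–22% |

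A separate set of assumptions, which included the health-centre ages on their own, gave 0.55–0.81 at the last age (type I error 11–28%) and 1.04–1.37 at 14 weeks. When the true covariance is compound symmetric, the ratio is 1.00 and coverage 95%; with the correct age-specific covariance, coverage is 95% at every age. The shortfall therefore comes from the covariance assumption and not from the method of checking.

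**The case against.** The strongest reply is that a journal article condenses, that residual covariance is usual analysis-plan content, and that the text names participant as a random factor without saying it is the only device for within-infant dependence. An unseen plan may add a residual structure. That is a fair limit on certainty. But the article goes beyond silence: it lists the terms of every model, and an analyst could run it as printed. The stated fallback responds to non-normal residuals, not to unequal variance or decaying correlation. A bootstrap that resamples participants could repair the intervals, but nothing ensures it would be triggered.

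Several stronger readings are tempting and do not stand:

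- *Intervals at 14 weeks are far too wide, so a real effect would be missed.* The excess is 2–13% with constant SD and reaches 18–48% only if the SD at least doubles. Any power loss depends on an effect size and SDs the article does not give.
- *Growth is analysed in raw units.* The scale is not stated.
- *The 24-month problem covers body composition.* Bioimpedance is done only at laboratory visits, the last at about 40 weeks.
- *The change "We changed the time for recruitment from 5–6 weeks postpartum to 6–7 weeks postpartum in August 2023" makes the model wrong.* It concerns recruitment timing. With randomised groups, neither that shift nor leaving out infant sex biases the contrast; at most, precision is lost.

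The quoted error rates are for unadjusted tests, whereas secondary outcomes are judged by q values. The rates measure how wrong the p values are and are not the planned decision rule's error rate.

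**Conclusion.** The point holds for the late ages. Read as written, the model understates the SE of the group difference at 24 months to roughly 0.5–0.8 of its true value (type I error about 11–36%), and at 40 weeks to about 0.6–0.8 if only laboratory visits are modelled. The direction was the same in every scenario and persists with constant SD, because falling correlation alone is enough. The exact size rests on assumed SDs, correlations, visit sets and complete data.

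Early-visit intervals are somewhat too wide, by an amount that cannot be fixed from the article. A reader might infer that the trial's main result is compromised; the documents do not support that. Infant growth is secondary, and this model is named for maternal and infant outcomes, so the primary 3′SL comparison is not shown to be affected. The matter is worth settling before analysis and is not a fault in the trial's core.

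**What to change.** For infant growth, keep the equal-baseline constraint and replace the random intercept with age-specific variances and an unstructured within-infant covariance, using Kenward-Roger degrees of freedom. State the fallback in advance: heterogeneous Toeplitz or autoregressive, or a random slope with heterogeneous residuals. Alternatively, keep a simple working model and report cluster-robust SEs with a small-sample correction.

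The fallback is needed. Nine health-centre ages require 9 × 10/2 = 45 covariance parameters, against 2 for the random intercept, with about 52 infants, so non-convergence is a real possibility. The four laboratory visits need 4 × 5/2 = 10. State also which ages enter which model and on what scale.

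Age- and sex-standardised scores at actual age are an optional gain in precision; as the constant-SD case shows, they do not cure the problem alone. The cost is wording and some added model complexity; no new data are required.
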